## Abstract

**Background:**

Child diarrhea persists as a leading public health problem in India despite evidence supporting zinc and low osmolarity oral rehydration salts as effective treatments. Across 2 years in 2010–2013, the Diarrhea Alleviation using Zinc and Oral Rehydration Salts Therapy (DAZT) program was implemented to operationalize delivery of these interventions at scale through private and public sector providers in rural Gujarat and Uttar Pradesh, India.

**Methods/Design:**

This study evaluates the cost-effectiveness of DAZT program activities relative to status quo conditions existing before the study, comparing a Monte Carlo simulation method with net-benefit regression, discussing the strengths and weaknesses of each approach. A control group was not included in the ‘before and after’ study design as zinc has proven effectiveness for diarrhea treatment. Costs will be calculated using a societal perspective including program implementation and household out-of-pocket payments for care seeking, as well as estimates of wages lost. Outcomes will be measured in terms of episodes averted in net-benefit regression and in terms of the years of life lost component of disability-adjusted life years in the method based on Monte Carlo simulation. The Lives Saved Tool will be used to model anticipated changes in mortality over time and deaths averted based on incremental changes in coverage of oral rehydration salts and zinc. Data will derive from cross-sectional surveys at the start, midpoint, and endpoint of the program. In addition, Lives Saved Tool (LiST) projections will be used to define the reference case value for the ceiling ratio in terms of natural units.

**Discussion:**

This study will be useful both in its application to an economic evaluation of a public health program in its implementation phase but also in its comparison of two methodological approaches to cost-effectiveness analysis. Both policy recommendations and methodological lessons learned will be discussed, recognizing the limitations in drawing strong policy conclusions due to the uncontrolled study design. It is expected that this protocol will be useful to researchers planning what method to use for the evaluation of similar before and after studies.

**Electronic supplementary material:**

The online version of this article (doi:10.1186/s13012-014-0164-2) contains supplementary material, which is available to authorized users.

## Background

Worldwide, diarrhea is the fourth leading cause of mortality among children under 5, accounting for 9% of total deaths [1]. In 2011, over 700,000 children died due to diarrhea [2], with eighty percent of cases occurring in East Asia and the Pacific, South Asia, and Africa, and 33% in South Asia alone [3]. However, diarrhea mortality is a solvable health problem, with this number of deaths having fallen from 4.6 million in 1980 [4]. India is a priority area for addressing the remaining burden, recognized as one of 15 countries that account for 53% of total episodes worldwide, with 312.22 million episodes and 205,600 deaths each year nationwide [2].

Since becoming widely used for diarrhea treatment in the 1980s [5], oral rehydration salts (ORS) have been instrumental in contributing to declines in prevalence. ORS prevents mortality by reducing the loss of fluids and electrolytes and death due to dehydration [6]. However, coverage of ORS in India remains low at less than 30%, and one out of ten children nationwide continues to experience diarrhea in any 2-week period [7].

The 2004 United Nations Children’s Fund (UNICEF)/World Health Organization (WHO) Joint Statement for the Clinical Management of Acute Diarrhea revised the global standards for acute diarrhea management to include ‘20 mg per day of zinc supplementation for 10–14 days (10 mg per day for infants under 6 months old)’ [8]. The therapeutic effect of zinc is to strengthen the immune system, improve absorption of water and electrolytes in the intestines, enhance the regeneration of the gut epithelium, increase levels of enzymes in the epithelium, and help the body clear pathogens from the intestines [9]. As a complement to ORS, zinc has been shown to reduce incidence [8], prevalence [10], and duration of diarrhea episodes [8],[9],[11]-[13]. Evidence on whether zinc reduces all-cause mortality is scarce, with one trial using non-injury mortality as a proxy for diarrhea deaths [9], not testing mortality as an outcome [11], or not having sufficient power to detect a significant difference in mortality [13]. Baqui et al. (2002) showed a non-significant difference in non-injury deaths, controlling for other factors, and authors concluded that the effect on mortality was due to zinc [9]. Applying the Child Health Epidemiology Reference Group (CHERG) Rules for Evidence Review indicates that mortality reduction could be as much as 23%, and ideal data, from randomized controlled trials (RCTs), is unlikely to emerge as the strength of evidence in support of zinc makes these trials unethical [14].

In India, evidence on the effectiveness of zinc for the management of acute diarrhea is mixed between studies showing an effect [10],[15],[16], and those with no or marginal effects [17]-[19]. Of these, one was conducted in a rural community setting [10]. This randomized controlled trial was carried out in six primary health care (approximately 30,000 population each centers) in Haryana [10], which provided an intervention that included training and supply of zinc and ORS to Anganwadi Workers and primary health center staff. This intervention nearly doubled the proportion of patients that received treatment between 3 and 6 months. In addition, the intervention led to significant reductions in diarrhea prevalence and the rate of hospitalizations due to diarrhea.

Building upon the success of effectiveness trial activities in Haryana, programmatic efforts to introduce zinc and ORS have been initiated throughout the last decade in India. Between 2005–10, the Point-of-Use Water Disinfection and Zinc Treatment (POUZN) project was implemented and found to be effective in improving both supply and demand for zinc. This program worked with pharmaceutical companies, channeled zinc through both the public and private sectors, collaborated with non-governmental organizations (NGOs), recruited support from key opinion leaders, provided training to detailers, stimulated prescribing practices among rural medical providers (RMPs), and promoted products with social marketing.

In 2010, the Diarrhea Alleviation using Zinc and ORS Therapy (DAZT) program expanded upon POUZN activities in scale and scope to make zinc and ORS available for the management of diarrhea through private and public sector providers in 6 districts of Gujarat and 12 districts of Uttar Pradesh (UP) states of northern India. DAZT is similar to POUZN in the characteristics mentioned above, but differed in that DAZT did not provide point-of-use water interventions, monitored zinc purchase and sales with short messaging service (SMS) in the private sector, and promoted zinc through informational booths in private clinics and hospitals. A full description of DAZT program activities is presented in Table 1.

**Table 1 Tab1:** **Diarrhea Alleviation through Zinc and Oral Rehydration Therapy (DAZT) Program Summary**

Sectors	Program activities
Public sector	Micronutrient Initiative (MI)
State-level policy changes	• Permission to implement DAZT was formalized through Memorandums of Cooperation between MI and the state government, and MI and the Department of Health and Family Welfare of Gujarat
	• In Uttar Pradesh, less formal permission was obtained from the government
	• Commitment from the Department of Women and Child Development in Gujarat
	• Both states added zinc to their NRHM guidelines and essential drug lists
Programmatic planning	National Rural Health Mission (NRHM) Program Implementation Plans (PIPs) were changed to include the procurement of zinc and ORS
Training	Three levels of training were conducted including (1) district level supervisors, (2) Block level supervisors and health workers, and (3) ASHAs and AWWs. Trios, a Delhi-based agency, conducted training in Gujarat, and three NGOs conducted the training in UP
Supply	• Supply was provided by two pharmaceutical companies including Healthy Life Pharma and FDC limited assuming that the public sector would treat 10% to 15% of diarrhea cases
	• Kits contained two ORS sachets and 14 taste masked zinc tablets, a measuring cup, and an informational leaflet for caregivers
Procurement	• Healthy Life Pharma and FDC limited provided the first procurement of kits
	• In Gujarat, in phase 1 (2011), MI provided ORS and zinc and in phase 2 (2012), MI limited its provision to zinc only (government procured ORS)
	• In 2013, the state governments disbursed funds to all districts to purchase zinc
	• ANMs may have used supply procured from sources other than MI
Incentives	Incentives were delivered to ASHAs, AWWs, and ANMs at monthly meetings to increase attendance rates
Distribution	• Supplies were distributed from Healthy Life Pharma to district medical stores, to district hospitals or block offices/CHC/PHC, to HSC-ANMs and CDPOs, to ASHAs and AWWs
	• ANMs informed PHC block level supervisors about needs; supplies were redistributed from areas of surplus to areas of shortage
Monitoring and supervision	• Supportive supervisors and MI divisional coordinators provided supportive supervision at the district, block, sub-center, and village levels in the form of data validation and capacity building
	• These mechanisms complemented existing monitoring mechanisms of the public health system
	• Supervisors attended monthly meetings of ASHAs, AWWs, ANMs, spent at least 18 days monitoring field staff visits, provided staff with hands on training when necessary, analyzed service provider knowledge and skills, stock status, and caregiver compliance with treatment
**Private sector**	**Family Health International-360 (FHI-360)**
Policy changes	• Memorandums of understanding were signed with prominent professional medical organizations (IAP, IMA, and other local medical associations)
	• Partnered with NGOs, pharmaceutical companies, and homeopathic and alternative medicine associations
Programmatic planning	An implementation plan was developed which involved a push and pull strategy—push: changed prescription among key opinion leaders in the medical community and created IEC materials with medical experts about diarrhea management and marketed ORS and zinc to RMPs and drug sellers; pull: natural demand creation for ORS and zinc within this group
Training	• NGO and pharmaceutical staff trained for three days in diarrhea epidemiology, importance of zinc and ORS, correct dosage and regulatory guidelines, and promotional strategies for effective product placement
	• Professional organization were provided with continuing medical education
	• DAZT corner staff were trained on selected topics from the three day training schedule
	• In UP, ten RMPs from the Sehat Mitra project were trained with an adapted version of the three day training session
Supply	Local manufacturers were linked with informal providers in designated areas
Procurement	Utopia Pharmaceuticals and Prayas manufactured and distributed zinc in UP, and RMPs procured zinc from West Coast Pharmaceuticals and generic brands from NGOs in Gujarat, with procurement plans accounting for different levels of demand according to season
Incentives	Pharma companies provided field representatives with commissions of 2 Rupees for each sale above 200
Distribution	Generic distributors supplied District Coordinator offices, which distributed to the Tehsil Coordinator based on demand
DAZT corners	Staffed informational booths in private clinics and hospitals to create awareness among caregivers and remind providers to prescribe zinc
Sehat Mitra project	In Faizabad Uttar Pradesh, a pilot project to provide ORS and zinc in patient’s homes by RMPs traveling on bicycles
Monitoring and supervision	• Monthly NGO and pharma staff meetings, validation of data and reports, SMS messaging from the field
	• FHI staff attended monthly meetings, district coordinators spent a lot of time in the field working with new staff

Accredited Social Health Activists (ASHAs); Anganwadi Workers (AWWs); Auxiliary nurse midwives (ANM); Child development project officer (CDPO); Community health centers (CHC); Diarrhea Alleviation and Zinc Therapy (DAZT); FDC Limited pharmaceutical company (FDC); Health subcenter (HSC); Indian Academy of Pediatrics (IAP); Indian Medical Association (IMA); Information, education, communication (IEC); Micronutrient Initiative (MI); Non-governmental organizations (NGO); National Rural Health Mission (NRHM); Oral rehydration salts (ORS); Primary health centers (PHC); Program Implementation Plans (PIP); Rural medical providers (RMP); Short messaging service (SMS); Uttar Pradesh (UP).

The objective of this study is to evaluate the cost-effectiveness of the DAZT program under real-world conditions compared to the status quo existing before the intervention was introduced in the study area. Two analytical approaches will be used to meet this objective: calculation of cost-effectiveness using a Monte Carlo Simulation method with patient level data [20], and calculation of cost-effectiveness using a net-benefit regression approach to control for covariates [21].

Both community-based [Lefevre et al. forthcoming, Bishai et al. forthcoming] and model-based evidence [4],[22] suggest that zinc supplementation to treat diarrhea is cost-effective in low- and middle-income countries (LMICs), although hospital-based studies do not find a significant difference in cost [23], effect [19], or both [24] between children receiving zinc and those that do not. These studies were conducted across a wide range of settings; however, none of them can be classified as implementation research. This study will evaluate the cost-effectiveness of the DAZT program and further discourse on approaches to economic evaluation of health programs in low- and middle-income countries. Methodologically, examples of cost-effectiveness analyses evaluating ‘before and after’ studies designs are emerging (for example [25],[26]); however, these types of studies are not well established in the literature. Thought is needed to identify special considerations that may be relevant to before and after study evaluations. The International Society for Pharmacoeconomics and Outcomes Research (ISPOR) has developed guidelines for using ‘real-world data’ [27], but guidelines for conducting cost-effectiveness analysis (CEA) alongside ‘before and after’ studies do not exist.

Alternative methods for conducting CEA are sometimes used to evaluate a single dataset to make methodological points, assess validity, and test robustness of results according to structural uncertainty [21],[28],[29]. Two of several analytical approaches available for CEA include Monte Carlo Simulation methods with patient level data [20] and net-benefit regression [21]. The latter framework combines established methodologies from economic evaluation and econometrics and has the advantage of being able to adjust for imbalances in confounding variables. Net-benefit regression methodology can be used for randomized [21],[30] and non-randomized studies [31],[32], although the case can be made that it is even more appropriate for non-randomized study designs as covariates are more likely to be unevenly distributed across study arms [33]. Bootstrapping confidence intervals presents the problem of ambiguity in incremental cost-effectiveness ratios (ICERs), although this problem can be circumvented in both methods using the net-benefit statistic, and both net-benefit regression and bootstrapping can be used to generate cost-effectiveness acceptability curves (CEACs). The bootstrap approach offers one advantage in that uncertainty around program costs can be simulated by resampling from parametric distributions fit to the data, while program costs are divided evenly across patients within each arm in the net-benefit regression approach [21] or are assumed to cancel out across study arms or phases [31]. Deterministic calculations and net-benefit regression are commonly evaluated in tandem in the literature [21],[31],[32], but scope exists to add thought on comparisons between bootstrapping and net-benefit regression. It is anticipated that documenting thought behind choosing between these analytic frameworks will be useful to researchers facing similar questions about evaluation of programs with similar study designs.

Policy recommendations from the completed research will add to the growing literature evaluating the cost-effectiveness of zinc for diarrhea treatment in low- and middle-income countries. Findings will be timely as India is developing a Health Technology Assessment (HTA) program in collaboration with the UK National Institute of Health and Care Excellence [34], in which the importance of CEA in policy making can be expected to increase. In addition, local capacity to produce zinc is rapidly expanding including Bharat Immunologicals and Biologicals Corporation Limited (BIBCOL), which is a government-owned corporation with the capacity to produce 240 million of 20 mg scored tablets of zinc sulfate per year [35]. Currently, about 40 private companies are producing zinc for local and international markets.

This article presents the DAZT program in India. Analytic methods for evaluating cost-effectiveness are described and compared, in addition to methods for assessing wealth quintile using principal components analysis. Strengths and limitations of the study are discussed, followed by arguments against targeting zinc according to subgroup, and considerations necessary for drawing conclusions about generalizability.

### Sample size and power calculation

The sample size for the main effects study was calculated according to standard methods for rates calculated through cluster randomized designs. Calculations used ORS coverage rates in the initial survey since very few children received zinc before the start of the program, and delivery of ORS and zinc were assumed to be linked. Actual sample sizes achieved for each survey are presented in Table 2. Using sample sizes from the main study, power to detect meaningful differences will be calculated for our cost-effectiveness estimate. Two formulas from Glick et al. [39] will be merged to determine power for cost-effectiveness using a novel approach to calculating the reference case ceiling ratio from an estimate based on per capita gross national income (GNI) and Lives Saved Tool (LiST) outputs of deaths averted/episodes averted.

**Table 2 Tab2:** **Sample sizes for each survey**

Survey	Number of participants		Dates
	Gujarat	Uttar Pradesh	
Starting point	4,200	3,889	March 22–May 10, 2011 Gujarat; April 1–June 21, 2011 Uttar Pradesh
Monsoon season			June through beginning of September^a^
Midpoint	1,072	1,790	September 1–October 8, 2012 Gujarat; May 24-October 4 2012 Uttar Pradesh
Endpoint	5,080	1,001	September 28–November 18, 2013 Gujarat; August 25–October 12, 2014 Uttar Pradesh

^a^Although peak diarrhea season lasts until November.

### Sampling and data collection

Data were collected through closed-ended survey questionnaires administered to a sample of caregivers of children 2–59 months old. In each survey, information was elicited on caregiver’s knowledge of diarrhea management, illnesses in the past 2 weeks, care seeking, treatment received, wealth quintile, and demographic characteristics of the household. Data on economic costs will be collected prospectively throughout implementation to capture program and incremental users' costs.

Program costs will be based on the financial records of the international NGOs working with public and private sector partners. To enhance generalizability, capital costs of furniture and equipment will be based on the original price paid inflated to 2014 and annualized using the full lifespan of the item and a 3% discount rate [20]. Donated labor, equipment, and facilities will be valued according to market prices; transfer payments such as taxes and subsidies will be removed; and rent costs will be used to represent building costs [40]. Since results will be presented in US$, it will not be necessary to adjust non-traded items to correct for price distortions [41]. Users' cost will be derived from reported out-of-pocket payments for care seeking and wages lost.

### Conceptual framework

A conceptual framework has been developed to identify important model variables based on categories from Andersen and Newman [42]. This framework consists of three main categories of interacting factors that are associated with treatment seeking including predisposing, enabling, and need factors; as indicated in Figure 1. The model was limited to only children that sought care for diarrhea, although other symptoms associated with diarrhea were assessed in caregiver surveys. If treatment was sought and given, economic costs could result, which are an important component of cost-effectiveness. In our framework, knowledge differs from the concept described in Andersen and Newman [43] in that our data describes awareness of the treatments, where they consider values and beliefs about treatment. All of these variables were justified by literature, and will be included regardless of whether their coefficients in our models are significant to ensure that variances are correctly estimated.

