**Table 3 Tab3:** **Variables to be tested**

Conceptual framework category	Parameter	Description
Demographic characteristics	Household size	Continuous variable (min = 2 people, max = 23 people in Gujarat and 32 in Uttar Pradesh)
	Child sex	Male =0, female =1
	Child age	Continuous variable (min =2 months, max =59 months)
Characteristics of the social structure	Mother’s education	No or primary education =0, primary education or above =1, secondary education or above =2, tertiary education or above =3
	Father’s education	No or primary education =0, primary education or above =1, secondary education or above =2, tertiary education or above =3
	Scheduled caste	Not a scheduled caste =0, scheduled caste =1
	Scheduled tribe	Not a scheduled tribe =0, scheduled tribe =1
	Other backwards caste	Not another backwards caste =0, other backwards caste =1
Caregiver knowledge	Knowledge about ORS	No knowledge =0, knowledge =1
	Knowledge about zinc	No knowledge =0, knowledge =1
Enabling factors	DAZT program	Initial survey, final survey
	Below poverty line card	No BPL card =0, BPL card =1
	Very poor	Any other wealth quintile =0, second wealth quintile =1
	Poor	Any other wealth quintile =0, third wealth quintile =1
	Less poor	Any other wealth quintile =0, fourth wealth quintile =1
	Least poor	Any other wealth quintile =0, fifth wealth quintile =1
Need factors	Duration of diarrhea	Continuous variable (min = 0 days, max = 15 days in Gujarat and 32 in Uttar Pradesh)
	Blood in the stool	No blood in the stool =0, Blood in the stool =1
Treatment seeking	Seek treatment outside of the home	No treatment sought outside of the home =0, treatment sought =1
Treatment given	Given ORS	No ORS =0, given ORS =1
	Given zinc	No zinc =0, given zinc =1

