## Discussion

Economic evaluation provides insights into the appropriate allocation of resources, and yet the number of cost-effectiveness and cost-utility analyses alongside programs at scale - where large amounts of resources are invested - remains limited. When planning these studies, differences in methods adopted have implications on the validity of findings and on their generalizability. Economic evaluation has traditionally focused on the cost of an intervention to produce a desired health outcome in studies based on modeled evidence or data collected alongside randomized controlled trials. As the number of interventions with known impact on health increases, there is an increased need for evidence on ways of operationalizing delivery of these health services to ensure high coverage, quality, and cost-effectiveness.

The aims of the DAZT intervention are to improve the supply, demand, and prescribing practices for treatment of diarrhea in children with zinc and ORS. These objectives are consistent with goals of The Indian Academy of Pediatrics [55], WHO [56], and UNICEF [3] who have all endorsed zinc supplementation to ORS for the treatment of diarrhea in children. In addition, the Government of India has established the Oral Rehydration Therapy Program to increase awareness about causes of diarrhea and its treatment among mothers and communities [7], and results of this study may be used to support this program.

This study will provide an evaluation of a zinc delivery strategy in a resource-constrained setting, in addition to a comparison of methods for cost-effectiveness analysis. The calculation of results using two different methods will provide evidence about the robustness of results, while informing broader discourse on methods for carrying out economic evaluations alongside programs delivered at scale. Each method has its strengths and limitations. The Monte Carlo Simulation with patient level data approach will allow for the incorporation of uncertainty around program costs and is a more widely used technique than the net-benefit regression approach. The net-benefit regression framework will allow for cost-effectiveness to be calculated controlling for other factors, which are unbalanced across arms in this study. Comparing the two analytical approaches will stimulate discussion about when analysts should choose one over the other when planning their analyses, particularly in the context of evaluation of programs at scale.

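### The net-benefit regression forces in variables the program is meant to change or that follow from it, so its treatment coefficient is at most a direct effect, not the incremental net benefit of DAZT

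*Protocol article*

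**What the plan says.** The Conceptual framework section gives the framework's purpose: "A conceptual framework has been developed to identify important model variables". It describes three groups of factors, explains how its notion of knowledge differs from that of the source model, and ends with the inclusion rule: "All of these variables were justified by literature, and will be included regardless of whether their coefficients in our models are significant". The stated reason is correct variance estimation.

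Table 3 arranges variables by framework category. Beside age, sex, household size, parental education, caste or tribe, below-poverty-line (BPL) card and wealth, it lists:

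- caregiver knowledge, of ORS and as "Knowledge about zinc", each coded "No knowledge =0, knowledge =1";
- duration of diarrhea, as a need factor;
- treatment seeking, coded "No treatment sought outside of the home =0, treatment sought =1";
- treatment given: ORS, coded "No ORS =0, given ORS =1", and zinc, coded "No zinc =0, given zinc =1".

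The program indicator (initial or final survey) stands in the same table.

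The section on net-benefit regression takes the coefficient on the start/endpoint variable as incremental net benefit and builds the cost-effectiveness acceptability curve (CEAC) from its one-sided p-values. The only reason it gives for adjustment is covariate imbalance in a non-randomized design. On the program itself, the Discussion says: "The aims of the DAZT intervention are to improve the supply, demand, and prescribing practices" for treating child diarrhea with zinc and ORS.

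**The concern.** Adjusting for imbalance is right for characteristics that differ between survey rounds for reasons other than the program. It is wrong for variables through which the program works. If demand generation raises knowledge, knowledge and prescribing raise zinc and ORS use, and zinc shortens illness, then a model that holds all of these fixed asks what DAZT does when none of them changes. The stated objective is DAZT against the status quo, which is a total effect.

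Two results depend on this: the regression estimate with its CEAC, and the comparison of the two methods, which the article calls its main strength. The Monte Carlo analysis derives its health outcomes from changes in ORS and zinc coverage entered into LiST, whereas the regression would hold ORS and zinc receipt constant. A difference between the methods could then be read as the result of confounder control when part of it comes from estimating a different quantity.

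**Working it through.** The article states no figure that depends on this choice, so there is nothing to reproduce. The check compares sections, then shows the algebra and an illustration.

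**1. What the article says elsewhere about these variables**

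| Table 3 variable | Other statements in the article |
|---|---|
| Knowledge of ORS and zinc | Caregiver knowledge is an outcome indicator (Setting and study design); informational booths are meant to raise caregiver awareness (Table 1) |
| Duration of diarrhea | Zinc shortens episodes (Background; Strengths and limitations) |
| Zinc given | Use of zinc is an outcome indicator (Setting and study design); hardly any child received it before the program (Sample size and power calculation) |
| ORS given | Part of the program's aim (Discussion); its delivery is assumed to be linked to that of zinc (Sample size and power calculation) |
| Treatment seeking | Outcome indicator (Setting and study design) |

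**2. Algebra, for an additive model**

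Let T = 1 at endpoint, X the background characteristics and M the knowledge, duration, zinc and ORS variables. Y is the modified net-benefit statistic (costs plus monetised outcomes, so lower is better).

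Y = α + βT + γX + δM + error.

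Let Δ be the change in M that the program produces and τ its total effect on Y apart from program cost. Then τ = β + δΔ. With mediated share s = δΔ/τ, β = τ(1 − s). Program cost c, spread evenly over endpoint children, adds cT to Y. The fitted coefficient is therefore τ(1 − s) + c, where the total is τ + c.

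Under the planned gamma model this split is exact only on an additive scale. The change in what the coefficient means does not depend on that.

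**3. Illustration**

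Sample sizes are those for Gujarat in Table 2 (4,200 and 5,080). Everything else is assumed:

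- knowledge rises from 5% to 50%;
- zinc use is 1% at start and 5% at endpoint, plus 40 points with knowledge;
- ORS use is 25%, plus 10 points at endpoint and 25 points with knowledge;
- duration is 4 days, less 1.0 with zinc and 0.3 with ORS;
- τ = −1.00 and c = 0, with linear regression on 30 data sets per scenario.

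| Assumed s | τ(1 − s) | Coefficient without M | Coefficient with M | Share kept |
|---|---|---|---|---|
| 25% | −0.75 | −0.996 | −0.746 | 74.9% |
| 50% | −0.50 | −0.998 | −0.497 | 49.8% |
| 75% | −0.25 | −0.999 | −0.247 | 24.7% |
| 100% | 0.00 | −1.006 | −0.005 | 0.5% |

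Adding an unmeasured common cause of duration and outcome gave shares kept of 75.3%, 49.4%, 24.5% and 0.0%, essentially unchanged. The number of sick children in the model would be smaller than these survey totals; that affects precision, not the expected coefficient.

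**4. Direction**

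Write the mediated part as −a + b, where a is the saving through shorter or milder illness and b the extra spending on zinc, ORS, consultation and transport, all of which Table 4 counts as costs. Holding M fixed moves the coefficient by a − b: against the program if a > b, in its favour if b > a. The article gives neither.

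**5. Care seeking**

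The Conceptual framework section limits the model to children who sought care. In that sample the care-seeking indicator is constant. A design matrix with intercept, program and care seeking has 3 columns but rank 2, so no care-seeking coefficient can be estimated. Conditioning then happens through the choice of sample instead.

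**6. Survey season**

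In Table 2 the start surveys ran March 22–May 10 (Gujarat) and April 1–June 21 (Uttar Pradesh). The endpoint surveys ran September 28–November 18 and August 25–October 12. The calendar periods do not overlap in either state, so in a start-versus-endpoint regression season is fixed by survey round.

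**The case against.** **The covariate list is inferred.** The inclusion rule does not cite Table 3. The table's one named use is descriptive, the regression section repeats no list, and Figure 1 is not available here. The framework has three main groups (predisposing, enabling and need), while Table 3 puts treatment seeking and treatment given in categories of their own. One can fairly read these last as consequences in the framework rather than forced covariates. This stands as a caution about ORS given and zinc given. It does not remove the point. The table contains the program indicator itself and four wealth dummies with the lowest quintile left out, which is how a regression list is built. Even on the narrow reading, knowledge is discussed within the framework just before the inclusion rule, and duration is a listed need factor.

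**Duration also reflects severity.** Severity may differ between rounds surveyed in different seasons, so dropping duration gives up some control. This stands as a cost of the fix.

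**Some benefit is not blocked.** The article cites fewer episodes in the 2–3 months after zinc treatment. Holding fixed the zinc given in the current episode does not remove that. This stands, and it is one reason not to assume full mediation.

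**The Monte Carlo analysis has no such covariates.** True, but its outcome is years of life lost. It softens the problem without replacing a correctly specified regression.

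**Conclusion.** The concern holds for knowledge and duration on any fair reading, and for ORS given and zinc given on the reading of Table 3 as the regression's variable list. If the plan is followed, the start/endpoint coefficient is at most a direct effect, plus program cost and any secular change, which the article acknowledges as a separate limitation. It should not be reported as the program's incremental net benefit.

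The size cannot be obtained from the article. The coefficient loses whatever share of the effect is mediated, and 25% to 100% is an assumed range, not an estimate.

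A reader might infer four stronger things that the documents do not support:

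- That the whole effect disappears. This is only the 100% row, which assumes that the program acts solely through these variables.
- That the bias must run against the program. Keeping program cost while removing mediated benefit pushes that way, but removing mediated spending on zinc and ORS pushes the other way.
- That care seeking is one of the harmful covariates. It drops out if the model is limited to care seekers; what remains is an inconsistency between the Conceptual framework section and Table 3, and selection on a variable the program may change.
- That collider bias adds to the problem. The check with an unmeasured common cause showed none, though in that set-up the program affected duration only through zinc and ORS, which were also held fixed.

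**What to change.** In the main net-benefit regression, and in every regression behind its CEAC, adjust only for characteristics the program cannot plausibly change: child age and sex, household size, parental education, caste or tribe, BPL card and wealth quintile. Move knowledge, duration, ORS given and zinc given to a separately labelled secondary or mediation model, and state that its program coefficient is not the incremental net benefit.

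Reconcile the Conceptual framework section with Table 3 on treatment seeking: either the model is limited to care seekers and the indicator is removed, or it is not limited in this way.

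Do not add survey season to the main model as a remedy, because it cannot be separated from the program variable in a start-versus-endpoint comparison.

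The change is one of analysis wording and needs no new data. The price is slightly larger residual variance and less control for differences in illness severity that duration may partly capture. The secondary model can show how much the latter matters.
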